### Study activities

#### Study preparation

**Community enumeration and randomization:** Prior to the initiation of the cluster randomized trial, we characterized the study communities using a combination of census data, health facility information, mapping and prospective demographic data. We identified communities of approximately 7500 people in three sub-counties of Migori County in western Kenya (population: 350,000, 65 government health facilities). Population estimates were calculated using the 2009 Kenyan census data with population growth estimates for 2015 and 2014, a method that was validated through door-to-door enumeration for a recent large-scale community randomized trial in rural western Kenya [41]. Eligible communities had at least one government health facility with capacity to provide HPV testing, support from community leaders for the community outreach and/or health campaigns, accessibility to health centers via a maintained transportation route and sufficient distance from other potential study sites to limit contamination between arms (buffer zones). As our target group is women in rural communities, we excluded urban settings or communities in which the nearest health center is Migori County Hospital and those that were taking part in a cluster-randomized trial of large-scale community-health campaigns for HIV-testing [41]. We conducted unmatched randomization using a random number generator on Stata 10. The unmatched design will allow us to consider the relationship between community-level factors and our outcomes of interest. After communities were chosen, population estimates were refined through household enumeration done by community health workers assigned to villages and sub-locations within the communities.
**Provider and key stakeholder focus groups:** Clinicians and community health workers (“providers”) within the community health campaigns and health facilities participated in focus group discussions to provide baseline data about perceived barriers and strategies to facilitate HPV screening uptake during the planning and implementation adaptation period of the study. Although we sought key stakeholder input throughout the development of the implementation strategies, we held three focus group discussions with key stakeholders in the intervention and control communities for Phase 1 (community chiefs, leaders of women’s groups, reproductive health coordinator, medical superintendent and Charge Nurse of Migori District Hospital). The goals of these focus groups were to obtain a group perspective on the intervention as planned for their communities, any anticipated challenges and strategies to optimize the screening strategy in both arms. Focus group discussions were analyzed using the theoretical domains framework, which mapped behaviors to intervention strategies, using evidence-based principles of behavior change [42].
**Training and finalization of the screening protocol.** We used educational modules piloted in western Kenya to provide standardized training in cervical cancer counseling and HPV-self testing to community health workers and clinicians [43]. The community health workers received training in community outreach messaging, delivery of the educational module in the community health campaign setting, and teaching women how to perform self-collection of HPV specimens. In addition to the general training, clinicians had undergone Ministry of Health-supported training to learn the cervical cancer screening protocol, including follow-up and pre-treatment exams. Two nurses who had undergone cryotherapy training were identified and supervised for ten cryotherapies at the County Hospital prior to study initiation.

#### Cluster randomized trial: Phase 1

After community enumeration, training and protocol finalization, we launched the cluster-randomized trial in the six control and six intervention communities in Migori County. (Figure 2) Phase 1 of the trial, consisting of the activities listed below, took place over the course of 1 year.
**Outreach and education:** In all communities, information about cervical cancer screening and the opportunity to learn more about HPV-based testing were provided through community outreach, including fliers, posters and brief informational sessions in markets, churches and women’s group meetings. Women and community leaders were provided with information on how to access cervical cancer screening in their community, e.g. location of clinic or timing and location of community health campaign. In all communities, women were invited to participate in a brief, standardized cervical cancer education module, either at the health campaign or in the health facility. The module is approximately 15 min and covers topics ranging from simple anatomy, definition of cervical cancer and HPV, how screening works, what treatment is available for precancerous lesions, and how to perform HPV self-testing.
**Community-based testing (intervention group):** In six communities randomized to community-based HPV testing, community outreach teams carried out two-week community health campaigns in which HPV-testing was offered through self-collection. In order to reach the entire community, the campaign moved to multiple sites over the two-week period, with approximately one to 2 days at each site. The campaigns consisted of health education and informed consent, after which a health worker provided additional instructions about self-collection and recorded a mobile phone number before dispensing the HPV testing kit. The woman then would go to a private area in the campaign tent to self-collect the specimen and returned the completed collection kit to the health worker prior to leaving.
**Clinic-based testing (comparison group):** In the six communities randomized to the control arm (clinic-based testing), women were directed through community outreach to go to their local health facility during regular clinic hours to carry out screening. At the clinic, a health worker offered the educational module, obtained informed consent and provided additional information about self-collection, and recorded a mobile phone number before dispensing the HPV testing kit and instructions.
**HPV testing:** While HPV test results are not the primary outcome for this study, the accuracy and reproducibility of measurements are essential for outcomes in both arms and for modeling the impact of the implementation strategies in larger populations. We tested the DNA for 14 HPV types (16, 18, 32, 33, 35, 39, 45, 51, 52, 56, 58, 59 and 68) using CareHPV™ testing system. Collected specimens were transported daily from the CHCs and weekly from the health facilities to the study lab at Migori County Hospital. Tests were run in batches of 90, with a turnover time of approximately 1–2 weeks for results.
**Notification of HPV results:** HPV test results were preferentially sent to women via text message with instructions about appropriate follow-up as recommended by the Kenya Ministry of Health guidelines. Messages were developed by key stakeholders and women from the target population during the focus group discussions. Women who did not have access to a phone, or did not wish to receive their results by SMS could opt for a return visit to the clinic, or a home visit.
**Standard referral for treatment (both arms, Phase 1):** Women who were HPV-positive were referred to Migori County Hospital for a visual exam with acetic acid and treatment with cryotherapy per the WHO guidelines [44].
**In-depth participant interviews and focus groups:** We conducted semi-structured interviews with randomly selected participants in both arms at three key points in the cervical cancer prevention cascade: screening delivery (*n* = 30), notification of results (n = 30) and treatment access (all). Participants were contacted either in person or by phone, and interviews conducted in person by experienced qualitative interviewers in the local language using interview guides developed by the research team. Topics explored in these interviews will elucidate ways to make cervical cancer screening more acceptable and accessible to women. Interviews captured quantitative data about women’s participation in various aspects of the prevention cascade. Interviewers then explored women’s perspectives of their experience with the intervention and explanatory factors related to the decisions to access screening and treatment through open-ended questions. Among women who did not access treatment, we probed for factors or strategies that would allow them to link to care in the future.
**Provider and key stakeholder interviews and focus groups:** During the cluster- randomized trial, providers in the community health campaigns underwent brief interviews at two time points: after three and six campaigns had been completed. In the clinic-arm, providers underwent interviews at three, 6 and 12 months into the intervention. These interviews will help to understand explanatory factors for the success or failure of the intervention from a health system perspective. Interview topics included personal attitudes and beliefs around screening importance and feasibility, perceived and actual barriers to implementation and potential strategies to overcome provider, health delivery and patient-level barriers to screening and treatment.

**Fig. 2 Fig2:**
[figure not shown]
Map of communities randomized to control and intervention activities in Migori, County Kenya. This map was developed by [name], who has provided written permission for use in this publication

#### Intervention development and cluster randomized trial: Phase 2

**Enhanced linkage to treatment:** We will work with health care providers, community members and other stakeholders to review outcomes from the quantitative, qualitative and process measures in Phase 1, critically examine and modify the cervical cancer *screening* strategy to develop and pilot the enhanced linkage to *treatment* intervention over a 6–9 month period between Phase 1 and 2. We will do this through a series of key stakeholder meetings, followed by the establishment of smaller working groups for the creation of the specific intervention components. In the first set of meetings, we will present the findings from Phase 1 and seek feedback on representativeness and discuss implications for culturally relevant intervention strategies. Options for the most feasible and acceptable strategies to increase the number of women linking to treatment will be explored in the light of that data.

Criteria for potential strategies include: community-developed, low-cost, feasible in all study communities, and able to ensure treatment for HPV-positive women in a timely manner in accordance with Ministry of Health guidelines. In a second, small stakeholder meeting, we will review potential strategies discussed and developed in the first meeting, and discuss solutions proposed in other settings, including the use of mobile treatment units, transportation vouchers, and treatment “navigators” to help women understand and travel to treatment sites. Once the linkage intervention has been defined, we will hold another working group with stakeholders to create a standardized protocol, training manual, standard operating procedures and data collection instruments. After equipment procurement, provider training and further outreach messaging, the enhanced linkage strategy will be piloted in two to three Phase 1 intervention communities prior to launch of Phase 2.

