**Fig. 1 Fig1:**
[figure not shown]
Two-phase cluster-randomized trial design

Development of an enhanced strategy for linkage to treatment: After Phase 1, we have an “inter-phase intervention development” period in which we are evaluating the results from the trial. The outcomes from the qualitative and quantitative measures will be used to refine the screening intervention using context-specific details and develop an enhanced strategy for linkage to treatment. Although we have identified factors that enable and inhibit women’s access to treatment, we chose to wait until after Phase 1 for the development of the enhanced strategy for linkage to treatment in order to truly work in partnership with the community. The delayed development of the linkage to treatment strategy has allowed us obtain a baseline measure of the efficacy of standard referrals and identify factors that would influence women’s access to care in this setting.

After developing the strategy for enhanced linkage, we will pilot and then test the linkage to treatment strategy as part of an “enhanced intervention” in the six communities that served as controls in Phase 1. Using these communities for the enhanced intervention increases the efficiency of the study in two ways: i. we will have done community enumeration and engagement, and ii. we will compare linkage to treatment outcomes from these “enhanced intervention” communities to the intervention communities from Phase 1.

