#### Primary and secondary endpoints

To determine the **reach** of cervical cancer screening using HPV-testing in community health campaigns compared to clinics, we are using the following metrics: i) the absolute number of women who completed screening in each arm and ii) the proportion of women in each arm who completed screening. The total number of women in each arm is the number of women 25–65 in each community as determined by census data. Secondary outcomes will include iii) the proportion of women who accept screening among women offered at each site and iv) the proportion of women in the clinic-based arm who request clinician-collected specimens.

To determine the **efficacy** of a community-developed strategy to increase treatment access, we will compare the efficacy of the community-based HPV testing with standard versus enhanced linkage to treatment using the following metrics: i) the number of women who receive treatment after screening HPV + in the intervention (Phase 1) compared to the enhanced intervention (Phase 2) and ii) the proportion of HPV-positive women in each arm who complete treatment. Secondary outcomes that address quality of care concerns for the models will include iii) the proportion of women who receive the correct treatment (per Ministry of Health protocol) during a single treatment visit and iv) the average time between HPV testing and access of treatment by arm.

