### Trial status

Focus Group Discussions and in-depth interviews with key informants took place in August and September 2015. A pilot campaign took place in December 2015. Screening activities and enrollment in Phase I of the cluster-randomized trial were carried out between January and September 2016. We are now sharing feedback of Phase I results and observations with various stakeholders (community members, health care providers, and health management teams) in preparation for FGDs and working groups, which are aimed at enabling us design a strategy for enhanced linkage to treatment.

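### Average time to treatment covers treated women only, and the efficacy endpoints have no common time limit from the HPV test in the two phases being compared

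*Protocol article*

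**What the plan says.** Under Study design and setting, the protocol article states that "we will compare linkage to treatment outcomes from these “enhanced intervention” communities to the intervention communities from Phase 1". Under Primary and secondary endpoints, the same contrast is measured by the number of HPV-positive women treated and by "the proportion of HPV-positive women in each arm who complete treatment". Neither metric has a time limit after the HPV test. A secondary outcome is "the average time between HPV testing and access of treatment by arm", with nothing said about women who are never treated.

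Under Statistical analysis, the efficacy model is a log-link Poisson model, within generalized estimating equations, whose offset is community size.

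On timing, the Phase 1 section says that "Phase 1 of the trial, consisting of the activities listed below, took place over the course of 1 year", and Trial status says that "Screening activities and enrollment in Phase I of the cluster-randomized trial were carried out between January and September 2016". Each campaign lasted two weeks. Providers were interviewed after three and after six campaigns, which indicates that the campaigns ran in sequence. The gap between phases is 6 to 9 months. The length of follow-up in Phase 2 is not given.

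The section on Phase 2 adds that "the enhanced linkage strategy will be piloted in two to three Phase 1 intervention communities prior to launch of Phase 2".

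**The concern.** The three features differ in weight.

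**Average time.** The outcome as worded can be computed only for women who reached treatment. The study expects enhanced linkage to change who reaches treatment, so the two means would describe differently selected groups. The metric can favour the arm that treats fewer women.

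**No common window.** The count and the proportion grow with the time allowed for treatment to occur. If that time differs between phases, or between communities within a phase, the difference in linkage mixes effect with follow-up. An offset for community size does not remove this.

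**Pilot in comparator communities.** Two or three of the six standard-linkage communities later receive the strategy under test. If Phase 1 treatments were still being counted then, enhanced-linkage treatments would be credited to standard linkage.

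At stake is whether the efficacy contrast and its timing outcome measure the linkage strategy itself.

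**Working it through.** The protocol gives an intracluster correlation of 0.11 for treatment, but no expected linkage proportion, HPV prevalence, effect size or follow-up length for this contrast. There is therefore no stated figure to reproduce. All rates and times below are assumptions, shown over a range.

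**1. Average time among treated women**

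Suppose 40 of every 100 HPV-positive women are treated at 30 days in both arms, and the enhanced arm treats x more at day d. No woman is treated later than she would have been otherwise.

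Mean in the enhanced arm = (40 × 30 + x × d) / (40 + x); in the standard arm it is 30 days.

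| x | d (days) | Calculation | Enhanced mean (days) |
|---|---|---|---|
| 10 | 90 | 2,100 / 50 | 42 |
| 25 | 60 | 2,700 / 65 | 42 |
| 25 | 90 | 3,450 / 65 | 53 |
| 25 | 120 | 4,200 / 65 | 65 |
| 40 | 90 | 4,800 / 80 | 60 |

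The enhanced arm looks 12 to 35 days slower. For x = 25 and d = 90, cumulative incidence among all HPV-positive women reads correctly: 40% v 40% at day 30, and 40% v 65% at day 90.

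**2. Unequal follow-up with no true effect**

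Assume the same constant linkage rate in both arms, with a proportion p treated by 6 months. The proportion treated by month w is 1 − (1 − p)^(w/6).

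| Months counted, standard v enhanced | p = 30%: standard v enhanced | p = 50%: standard v enhanced |
|---|---|---|
| 12 v 6 | 51% v 30% (−21 points) | 75% v 50% (−25 points) |
| 3 v 6 | 16.3% v 30% (+13.7 points) | 29.3% v 50% (+20.7 points) |
| 6 v 6 | 0 | 0 |

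Differences are enhanced minus standard. The sign depends on which arm is followed longer, and the protocol does not settle that.

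A calendar close would not give equal follow-up even within Phase 1. Assume capture closed in December 2016, at the end of the stated year. Women screened in January would have about 11 to 12 months and women screened in September about 3. If the campaigns were spread over that whole period, identical linkage would show as roughly 51% in the earliest community and 16% in the latest (p = 30%), or 75% and 29% (p = 50%).

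**3. Whether the pilot can reach the Phase 1 count**

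- Share of comparator communities that receive the pilot: 2/6 = 33% to 3/6 = 50%.
- Enrollment closed in September 2016. The article describes protocol version 3.0 of 20 July 2017, and its Trial status section says the linkage strategy was still to be designed. Taking that status as of July 2017, every Phase 1 woman was about 10 (September 2016) to 18 (January 2016) months past screening before a pilot could start.
- Pilot-period treatments can therefore enter the comparator only if Phase 1 treatment is counted beyond about 10 months.

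If it were, assume true linkage of 40% v 70%, equal numbers of HPV-positive women per community, and a pilot that closes a fraction f of that 30-point gap in k communities. Observed difference = 30 − (k/6) × f × 30.

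| f | k = 2 | k = 3 |
|---|---|---|
| 0 (Phase 1 closed first) | 30 | 30 |
| 0.25 | 27.5 | 26.25 |
| 0.5 | 25 | 22.5 |
| 1 | 20 | 15 |

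The loss runs from nil to 15 points, entirely on assumed inputs.

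**The case against.** The tempting stronger reading is that the standard-linkage arm does get longer follow-up and is contaminated by the pilot. A reader might infer this from the pilot's location, but the protocol does not support it. The abstract describes Phase 1 as over. The Phase 1 section gives it one year. The design section treats a baseline for standard referral as already obtained, and Phase 1 results were being fed back to stakeholders before the strategy was designed. Nothing says that pilot-period treatments are added to the Phase 1 count, or that the pilot serves women already counted rather than newly screened ones. Longer follow-up of the standard arm cannot be asserted either, because Phase 2 follow-up is not given. Both effects, where they occurred, would work against the study's own hypothesis. All of this stands.

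It is also fair that this is a condensed article. A window or data cut-off may be set in the full protocol or analysis plan, so its absence here carries little weight taken alone.

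On average time, the defence is that the outcome is secondary, sits beside the proportion of all HPV-positive women treated, and might be analysed by time-to-event methods. The proportion would indeed reveal the difference in linkage. However, the outcome is worded as an average by arm, and a mean among treated women stays a selected comparison whatever is reported beside it. Nor does closing Phase 1 on a calendar date answer the follow-up point, because screening was staggered over nine months.

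**Conclusion.** The point holds in a limited form. The average-time outcome is badly defined as stated: it is conditional on treatment and can make the arm that links more women look slower, by 12 to 35 days in the assumed examples. The count and proportion have no common time limit in this document, and the stated offset does not correct for follow-up. With staggered Phase 1 screening and an unstated Phase 2 follow-up, unequal ascertainment is possible in either direction. On the assumed constant rates, the spurious difference ranges from 25 points against enhanced linkage to about 21 points in its favour.

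The pilot overlap is a fact of the design, but contamination is not shown. It would require Phase 1 counting to run past about 10 months, and its size would then be an assumption. If Phase 1 is closed before the pilot, it is zero.

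**What to change.** Define efficacy as treatment within one fixed window after each woman's HPV test, identical in Phase 1 and Phase 2. Choose a window short enough to end, for every Phase 1 woman, before the pilot starts in the comparator communities. A window of 6 months, for example, would have closed around March 2017 for the last women screened. With the same window for everyone, no follow-up term is needed in the model.

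Replace average time with the cumulative incidence of treatment over that window among all HPV-positive women, with untreated women censored at its end and clustering by community allowed for.

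The cost is small. The change is to endpoint wording, and the average-time outcome already requires the test and treatment dates. Some late treatments leave the primary count; they can be reported separately. Phase 2 must keep recording treatments for the full window after its last HPV test.

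If the full protocol or analysis plan already sets such a window and a Phase 1 cut-off, the article need only state them, and the change to average time remains.
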